### **5 Methods**

#### **5.1 Characteristics of the study**

This is a randomized clinical trial, which will consist of two groups, and developed at the Department of Physiotherapy at the Federal University of Rio Grande do Norte.

## 5.2 Sample

Forty-six individuals with a clinical diagnosis of unilateral tendinopathy of the supraspinatus and/or infraspinatus tendon by means of ultrasonography (US) or nuclear magnetic resonance (NMR) exams, between 18 and 60 years of age, of both sexes will participate in this study. They will be randomly divided and allocated into two exercise groups, with 23 individuals each: 1) isometric group, which will undergo an isometric resistance training protocol for the RC musculature associated with a stretching and strengthening protocol focused on the periscapular musculature; and 2) isotonic group, which will undergo an isotonic resistance training protocol for the RC musculature associated with a stretching and strengthening protocol focused on the periscapular musculature.

Sampling will be non-probabilistic type of consecutive cases, where individuals will be recruited from a waiting list for physiotherapeutic care in the Physical Therapy Department of UFRN and through dissemination carried out at UFRN, in the city of Natal-RN and social media through posters. The sample size was determined considering the main outcome variable, pain with arm elevation without load, considering a difference between means of 2.05 and standard deviation of 2.30 in the numerical pain rating scale (NPRS) (34). Adopting a 80% Power and  $\alpha = 0.05$ , at least 21 individuals per group will be required. Considering possible sample losses of approximately 10%, the sample should be at least 23 individuals per group.

This project will be sent to the Ethics and Research Committee of UFRN (CEP/UFRN), through the registration in Plataforma Brasil, and will only start its activities after approval. All volunteers will receive a verbal and written explanation of the objectives and methodology of the study, as well as its risks and benefits; and those who agree to participate must sign an informed consent form, in accordance with Resolution 466/12 of the National Health Council, confirming their participation in the study. The project will be submitted to the Brazilian Registry of Clinical Trials (<http://www.ensaiosclinicos.gov.br/>) before

starting to recruit individuals.

### 5.3 Eligibility Criteria

Individuals of both sexes aged 18 to 60 years, with a history of shoulder pain for more than 3 months, and with a clinical diagnosis of rotator cuff tendinopathy by means of US or MRI exams, performed by a physician, will be included in the study (4).

Then, a physiotherapist with 6 years of experience will carry out an evaluation of the recruited individuals with the collection of personal data and clinical history, and physical examination, which will consist of palpation of the rotator cuff tendons, evaluation of the amplitude of the painful arc during arm elevation in the three planes of active and resisted shoulder movement, and the performance of the following special tests to detect dysfunction in the supraspinatus and infraspinatus tendons: Jobe's test to assess supraspinatus tendon injury (35), resisted external rotation for infraspinatus injury (36), apprehension and replacement tests for injury in the posterior-superior portion of the infraspinatus, characteristic of internal impact (35).

The diagnosis of RC tendinopathy will be performed by an orthopedic surgeon specialized in the shoulder complex, according to the clinical history, physical examination and morphological alterations of RC tendons, visualized by means of MRI or US: hypoechogenicity of the tendon and /or thickening of tendon fibers with or without bursal thickening (37).

Individuals will be excluded if they practice sports activities with high demand on the upper limbs; have impairments in the long head of the biceps; adhesive capsulitis (38); have history of symptom onset due to glenohumeral dislocation or subluxation, or fracture of the clavicle, scapula, or humerus (39); history of surgical stabilization or repair of the rotator cuff (40); signs of partial or complete rupture of the rotator cuff (12,40); neurological disorders (41); use of corticoid injection 3 months before the evaluation (39) and body mass index (BMI) > 28 kg/m^2, since this can compromise the quality of the electromyography data (39), and individuals who are using antibiotics from the class of fluoroquinolones (42) and/or with diabetes (43), as both affect tendon metabolism.

#### 5.4 Evaluation procedures

All included individuals will undergo the following assessments: a) pain and general function of the shoulder complex; b) electromyographic activity of the shoulder complex musculature during maximal isometric contractions; and c) electromyographic activity of the shoulder complex muscles during arm elevation in the scapula plane.

This evaluation sequence will be carried out in three moments: 1) initial evaluation, immediately before the first intervention session; 2) immediately after the first exercise session; and 3) after six weeks of intervention. All evaluations will be carried out by an evaluator who will not know which intervention group the individuals belong to (blind evaluator), with the interventions applied by two other trained researchers.

One week before the initial assessment, individuals will be randomly allocated using the online randomization tool for randomized clinical trials, available on the website ([www.randomization.com](http://www.randomization.com)). To guarantee the confidentiality of the allocation of individuals, this will be carried out by one of those responsible for applying the intervention, who will be the only one to know which group the individuals belong to. After determining the group, individuals will be introduced to the evaluation process and equipment, and will undergo a test to determine the elastic band to be used during periscapular muscle strengthening exercises. In addition, individuals allocated to the isometric or isotonic exercise group will perform the initial load determination test for each of the exercises. The sequences of the study procedures are described in Figure 1.

[figure not shown]

**Figure 1.** Study's flowchart.

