### 5.5 Intervention Protocol

Individuals from each group will perform an exercise session according to their group (isometric and isotonic) on the day of baseline assessment in order to verify the immediate effects of exercises. Then, they will participate in a six-week intervention, twice a week, in order to verify the effects of a strengthening program directed at the RC. Exercises will be performed on both limbs.

Individuals from all groups will undergo a protocol for stretching and strengthening the periscapular musculature following the protocol used by Camargo et al (53), which consists of stretching the upper trapezius and pectoralis minor muscles and the posterior portion of the shoulder, and strengthening the serratus anterior and lower trapezius muscles.

The evaluation to determine the initial loads of the exercises will be carried out one week before the baseline evaluation and beginning of the interventions. At that moment, participants will also familiarize themselves with each exercise with light resistance and will be guided by the evaluator to perform the technique correctly. In order to adjust and progress the exercise load over the six weeks of intervention, the assessments will be repeated in the third and fifth weeks of intervention, as shown in Figure 2 with the flowchart of the intervention procedures and progression of each group.

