**c) Não coloque sua barra "/" fora dos marcadores finais.**

Você deverá indicar no questionário a intensidade do sintoma que você sentiu nesta última semana com relação a seu ombro afetado. Se você não tiver certeza sobre o ombro que está envolvido ou se você tiver quaisquer outras dúvidas, pergunte antes de preencher o questionário.

Se, por algum motivo, você não entender uma pergunta, procure as explicações que estão incluídas no final desse questionário.

**Se um item não se relacionar a você ou se você não o tiver sentido nesta última semana, imagine qual seria sua resposta mais adequada para tal.**

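### Baseline pain, PSS and WORC are measured a week after randomisation and after load testing, and allocation concealment is not assured

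*Combined protocol and SAP*

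**What the plan says.** **Order of events.** Section 5.4: "One week before the initial assessment, individuals will be randomly allocated using the online randomization tool for randomized clinical trials". Once the group is determined, participants are shown the evaluation process and equipment, take an elastic-band test, and take the initial load test for their allocated exercises. Section 5.5 agrees on timing: the load evaluation "will be carried out one week before the baseline evaluation and beginning of the interventions", with familiarisation with each exercise at the same visit. Outcomes are first measured at the "initial evaluation, immediately before the first intervention session".

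**Who allocates.** The stated aim is "To guarantee the confidentiality of the allocation of individuals". The means is that "this will be carried out by one of those responsible for applying the intervention, who will be the only one to know which group" each participant belongs to. The same section describes a blind evaluator, "with the interventions applied by two other trained researchers". No list holder, envelope or central release is described. Section 5.3 gives eligibility assessment to a physiotherapist and does not say whether this is the allocating researcher.

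**What is measured.** Section 5.2 names pain on unloaded arm elevation (NPRS) as the main outcome. The WORC form (Anexo II) asks about "a intensidade do sintoma que você sentiu nesta última semana com relação a seu ombro afetado", that is, symptoms of the affected shoulder over the past week.

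**Analysis.** Section 5.7 plans two-way repeated-measures ANOVA, or Friedman if the data are not normal. It gives no baseline covariate and no rule for missing data.

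**The concern.** A baseline protects a randomised comparison because it cannot have been affected by the assignment. Here a week passes between assignment and baseline, and in that week participants do things that depend on their arm. Section 5.5.2 bases the load on maximum isometric strength against a dynamometer, and section 5.5.3 bases it on 8 RM with dumbbells. Expectation, or soreness after testing, could move self-rated pain, PSS or WORC differently in the two arms before the first outcome is recorded. No later analysis can recover the missing pre-randomisation value.

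Two further things are at stake. Anyone who leaves during that week has been randomised but has no outcome data at all. And if the researcher who runs the allocation also has a say in who enters or when, entry could depend on the coming assignment. The protocol describes nothing that would prevent this.

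**Working it through.** **1. The plan's own figure.** Inputs from section 5.2: difference 2.05, SD 2.30, power 80%, alpha 0.05 (two-sided assumed, since sidedness is not stated).
- Standardised difference = 2.05/2.30 = 0.891. An exact two-sample t-test needs 20.77, so 21 per group, as stated. Power is 80.5% with 21 per group and 84.0% with 23.
- Loss allowance: 21/0.9 = 23.3, which rounds up to 24 against the stated 23. The 23 covers losses of 2/23 = 8.7%, close to the stated 10%.

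The sample size reproduces, and the timing of baseline does not change it. The 2.05 serves below only as a yardstick.

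**2. The sequence, side by side.**
- Week -1: allocation (5.4).
- Week -1, after allocation: load test and familiarisation (5.4, 5.5).
- Day 0, before the session: first outcome measurement (5.4).
- Day 0, after the session: second measurement.
- Six weeks: third measurement.

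The seven-day recall of the baseline WORC therefore covers the week that begins with allocation and load testing.

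**3. What the planned analysis does with a baseline shift.** The six-week part of the group-by-time comparison is

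(six-week mean - baseline mean, isometric) - (six-week mean - baseline mean, isotonic).

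Suppose events after allocation move baseline by d points more in one arm, and a fraction p of that shift remains at the later measurement. The contrast is then wrong by d(1 - p) in absolute value; the sign depends on which arm moved and in which direction. The documents give neither d nor p. Taking 0.5 points as an assumption, with half and double of it as a range:

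| d (assumed) | p = 0 | p = 0.5 | p = 1 |
|---|---|---|---|
| 0.25 | 0.25 (12% of 2.05) | 0.125 (6%) | 0 |
| 0.5 | 0.5 (24%) | 0.25 (12%) | 0 |
| 1.0 | 1.0 (49%) | 0.5 (24%) | 0 |

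For the same-day contrast, p is the fraction still present just after the session. A shift that lasts through the session cancels.

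**4. Passages that do not fit together.**
- Section 5.4 makes the allocating researcher the sole holder of the group, yet has two researchers deliver the interventions. Anyone who delivers an exercise knows the arm.
- Section 5.5.2 says the isometric maximum is determined during the strength assessment described earlier, which is the outcome assessment of 5.4.2. Taken literally, this conflicts with the week -1 timing in 5.4 and 5.5. On that reading only the isotonic arm has an arm-specific maximal test before baseline; on the other reading both arms do. On both, allocation and the isotonic load test precede baseline.
- Section 5.5 has the evaluator guide technique at familiarisation. If this is the blind evaluator of 5.4, blinding may be lost before the first measurement.

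**The case against.** The strongest reply is that concealment concerns whether the person deciding entry can foresee the next assignment, and nothing says the allocating researcher enrols anyone. Screening belongs to a physiotherapist, diagnosis to an orthopaedic surgeon, and section 5.4 states a confidentiality aim. A reader might infer that allocation is openly unconcealed, or that the treating researcher can steer participants between arms. The documents do not show that. They show only that no safeguard is described and that the enroller is not identified as a different person.

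Other stronger readings also go too far:
- That participants know their arm at baseline. No section says they are told. It is an inference from the different tests and from consent that covers the methodology (5.2).
- That the treatment effect is biased by some stated percentage. A shift must differ between arms, last a week after one test visit, and then fade. None of this is documented.
- That the WORC recall window affects the main outcome. It does not: the NPRS is asked after the tests (5.4.2), not recalled over a week.
- That withdrawals in the interval exhaust the sample. The margin is 23 - 21 = 2 per arm whenever people leave, so this is not specific to the timing. An earlier baseline would not supply their missing outcomes either.

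Figure 1, which is said to describe the sequence of procedures, is not available in the text reviewed and might clarify some of this. What stands against all these replies is the written order: assignment, load testing and familiarisation, and only then baseline.

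**Conclusion.** The concern holds for the order of events and, in a limited form, for concealment. That baseline follows randomisation is a written rule in section 5.4, and section 5.5 supports the timing of the load test. That a shift enters the six-week contrast follows from the planned ANOVA. How large it is, and in which direction, cannot be determined: it could be zero, and the values in the table are conversions of assumed shifts, not estimates. For concealment, the supportable statement is that it is neither assured nor documented. The conflicts between 5.4, 5.5 and 5.5.2 need to be reconciled by the sponsor. This should be corrected because the loss cannot be repaired at analysis and the change is small. It does not by itself invalidate the comparison.

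**What to change.** - **Order.** At the existing week -1 visit, collect NPRS on unloaded elevation, PSS and WORC first. Only then reveal the allocation and do any load test or familiarisation.
- **Analysis.** State in section 5.7 that these values are the baseline for the six-week comparison. Keep the day-0 pre-session NPRS as the reference for the immediate effect only.
- **Allocation.** Generate the whole sequence once, in advance. Have it held in sequentially numbered, opaque, sealed envelopes by an existing team member who does not screen, treat or assess. Open each envelope only after the week -1 measures are complete. The documents do not identify such a person, so the sponsor must name one.
- **Text.** Reconcile the sole-holder statement with the two treating researchers. State when the isometric maximum is determined, and say whether the evaluator who guides familiarisation is the blind evaluator.

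**Cost.** A longer week -1 visit (roughly 20-30 minutes, an estimate not taken from the documents) and a set of envelopes. No extra visit is needed and the sample size is unchanged. Baseline EMG remains post-allocation unless it is moved too, and this should be stated as a limitation. If NPRS is taken at week -1 without the maximal contractions that belong to the later assessments, change within each arm mixes two testing conditions. The comparison between arms does not suffer, because the difference is the same in both.

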#### 5.4.1 Pain and function assessment

To assess shoulder pain and function, the Brazilian version of the Penn Shoulder Score (PSS) questionnaire will be used, which includes the domains of pain, satisfaction and function. The pain and satisfaction domains have, respectively, three items (pain at rest, pain during normal activities, and pain during strenuous activities) and one item (satisfaction with the current level of shoulder function) assessed using a numerical rating scale (NPRS) from 0 to 10, where 0 corresponds to no pain and not satisfied, while 10 corresponds to the worst possible pain and very satisfied. The function domain contains twenty items, graded on a four-point Likert scale, ranging from 0, which means “I can't do it at all”, to 3, “with no difficulty”, with a maximum score of 60 points. The PSS score ranges from 0 to 100 points, where the maximum score (100) indicates no pain, high satisfaction and good function (44).

In addition, aspects of quality of life will be evaluated through the Brazilian version of the Western Ontario Rotator Cuff Index (WORC) questionnaire, developed and validated for individuals with RC dysfunction, consisting of 21 items in five domains regarding life and health (physical symptoms, sport/recreation, work, lifestyle, and emotions). Each item has the same weight and varies from 0 to 100 (100 mm on a visual analogue scale - VAS), and the total of the questionnaire varies from 0 to 2100 mm, which are converted to a score of 100%, where 0% means the worst possible score and 100% implies no reduction in health-related quality of life (45).

#### 5.4.2 Assessment of electromyographic activity during maximal isometric contraction and during arm elevation

The maximum isometric contractions will be performed with a dynamometer (Nextech, DFS-X1000, Nextech Global Company Limited, Thailand), which will be fixed in an apparatus that guarantees isometric contraction, and individuals will be instructed to push against the dynamometer for arm elevation and external and internal rotations as hard as possible. For arm elevation, individuals will be sitting in a chair with back support and shoulder to 90° of elevation in the scapular plane. For shoulder external and internal rotation, individuals will be sitting, shoulder positioned at 0° abduction, flexed elbow 90°

and fist in neutral position (34). Individuals will be verbally encouraged and maintain contraction for five seconds. Each test will be performed twice, with a two -minute interval between attempts, and the average values will be used in the analysis.

For arm elevation individuals will be standing and will perform arm elevation in the scapular plane (40° of humeral abduction) using a flat vertical surface as a reference. On this same surface will 30, 60, 90 and 120 degrees of elevation will be marked for each individual. After that, individuals will perform arm elevation in each of these angles with and without load, supporting a weight of 1.5 kg for those with less than 68 kg body weight and a weight of 2.5 kg for those who with more than 68.1 kg body weight (13).

During the maximum isometric contractions and arm elevation in the different angles with and without load, the electromyographic signal of the lower trapezius, serratus anterior, middle deltoid, and infraspinatus will be collected.

For the acquisition and processing of electromyographic signals, a signal an 8 channels (EMG System do Brasil®) conditioner module (MSC 1000) with digital analog converter - A/D (CAD, 12/36-60 K) with 12 bits resolution will be used. The equipment has a common rejection ratio (RMC) greater than 80 dB, with 2,000 Hz sampling frequency and the filtrate signal between 20 and 500 Hz. As the gain programmed in the converter is 50 times and 20 times in the electrodes, the signals will be amplified 1000 times. The electromyographer will be fed by a battery and connected to a notebook that will receive the signal and store it in file. EMGLAB (EMG System from Brazil®, Brazil) software will be used for digital signal analysis.

Active surface electrodes composed of an Ag/AgCl system associated with a conductive gel, simple differential, of bipolar configuration with dimensions of 4 cm X 2.2 cm of adhesive area and 1 cm of conductive area separated by 2 cm between electrode will be used (Miotec®, Brazil). A reference electrode of monopolar configuration will also be used, composed of an Ag/AgCl system associated with a conductive gel, with a diameter of 3.8 cm of adhesive area and 1 cm of conductive area (Miotec®, USA).

The positioning of sensors for the evaluation of lower trapezius, serratus anterior, middle deltoid and infraspinatus will follow the procedure described in

Michener et al. (46). A reference electrode will be attached to the ulnar styloid process on the contralateral side (48). Before placing the electrodes, the skin of the assessed regions will be shaved and cleaned with alcohol. The electromyographic activity will be evaluated only in the muscles of the symptomatic side, and after the tests, the individuals will be questioned about their pain, using the Numerical Pain Rating Scale (0-10, with 0 being no pain and 10 being the worst possible pain). (49).

To evaluate the amplitude of the electromyographic signal of each muscle and subsequently measure the muscle activation ratio between muscle pairs, the raw data will be filtered at a bandpass frequency of 20-450 Hz, rectified and smoothed using an algorithm of root mean square (RMS) with a 50-millisecond moving window, using Matlab software.

The ratio of muscle activation between the following pairs will be evaluated: 1) infraspinatus and middle deltoid; 2) infraspinatus and lower trapezius; and 3) lower trapezius and serratus anterior. These muscle pairs were selected since individuals with RC dysfunction have increased compensatory activity of the middle portion of the deltoid (14–16) and incoordination between the lower trapezius and serratus anterior and between the upper and lower portions of the trapezius (13).

